### Additional consent provisions for collection and use of participant data and biological specimens {26b}

Permission for the research team to share relevant data will be obtained from participants. Participants will also be asked whether they agree to use their data if they withdraw from this trial. In addition, the participants will be provided opportunities to ask any questions about the use of analgesia pump use and data collection. The REDUCE trial will not involve the collection of biological specimens.

## Interventions

### Explanation for the choice of comparators {6b}

A meta-analysis pointed out that perineural administration of dexamethasone as an adjuvant to bupivacaine, but not ropivacaine, could slightly prolong the duration of analgesia [35]. Due to the elevated pH of dexamethasone and the incompatibility of ropivacaine with alkaline solutions, in vitro study observed rapid crystallization with a mixture of dexamethasone and ropivacaine. Therefore, the combination of dexamethasone and ropivacaine should be used with caution. The combination with dexamethasone and bupivacaine did not observe such phenomenon and will therefore be used in the REDUCE trial.

### Interventions description {11a}

#### Intervention and control groups

After the initiation of the study, eligible participants will be consecutively screened for trial inclusion. A total of 156 participants will be randomly assigned to one of the two groups using a computer-generated list.

The control group will receive scalp nerve blocks with 0.5% bupivacaine 21 ml with epinephrine at 1:200,000, plus normal saline 1 ml.

The DEX_4mg_ group will receive scalp nerve blocks with 0.5% bupivacaine 21 ml with epinephrine at 1:200,000, plus 4 mg dexamethasone (1 ml).

An independent researcher will prepare the study solution in a separate operating room. After opening the envelope containing the treatment allocation, the study solutions will be prepared in 50-ml syringes for scalp nerve blocks with 23-gauge needles and will be numbered by an independent researcher. After induction, the assigned solutions will be used for nerve blocks injections by the anesthesiologist, who will be blinded to the group allocations.

#### Anesthesia protocol

All participants will be informed about the REDUCE trial during a pretreatment visit. Each participant will be equally randomized to one of the groups using a closed envelope technique. After the patient arrives in the operating room, standard monitoring, such as a 5-lead electrocardiogram, heart rate (HR), pulse oximetry, and noninvasive arterial blood pressure (BP) will be recorded. Induction will be carried out with 2 to 3 mg/kg propofol and 0.3 to 0.5 μg/kg sufentanil. Neuromuscular blockade will be performed with 0.6 mg/kg I.V. rocuronium to facilitate tracheal intubation.

After induction, anesthesia will be maintained with 4 to 8 mg/kg/h propofol and 0.1 to 0.3 μg/kg/min remifentanil at the discretion of the attending anesthesiologist. Remifentanil will be adjusted according to the degree of surgical stimulation. Additional boluses of remifentanil (0.5 μg/kg/bolus) will be administered to decrease any significant response to surgical stimulation. Meanwhile, the infusion rate of remifentanil will be increased by 0.05 μg/kg/min. No additional sufentanil will be used intraoperatively. We will use mechanical ventilation through an endotracheal tube with a mixture of oxygen in air (fraction of inspired oxygen (FiO2) 0.5 to 0.6) with end-tidal carbon dioxide between 35 and 45 mmHg. The intraoperative HR and BP will be maintained within 20% of the baseline levels. An increase or decrease in the mean arterial pressure (MAP) from the baseline value by more than 20% will be considered clinically significant and will be treated with nicardipine or dopamine. Nicardipine or dopamine will be administered with intermittent boluses and with continuous infusion if necessary. The number of patients who receive nicardipine or dopamine will be recorded. The intraoperative HR and BP will be recorded before anesthetic induction, after anesthetic induction, 5 min after intubation, and at the insertion of cranial pins, skin incision, skull drilling, dura mater opening, and skin closure. Similarly, any significant elevation or reduction in HR and BP will be noted throughout the operation. The dosages of all drugs and intraoperative physical parameters will be closely monitored and recorded by the investigator.

After surgery, neostigmine (0.05 mg/kg) and atropine (0.02 mg/kg) will be administered to reverse residual muscle relaxation. Ondansetron (8 mg) as an antiemetic prophylaxis will be intravenously administered. Extubation will be performed when the standard extubation criteria, such as eye opening, adequate spontaneous respiration, and purposeful movements, have been met.

#### Scalp nerve blocks

The anesthesiologist will perform scalp nerve blocks based on the group allocation 10 mins before the incision. Scalp nerve blocks will be performed according to the technique previously described by Pinosky et al. [14]. The following nerves will be blocked bilaterally: the supraorbital and supratrochlear nerves will be blocked with 2 ml of solution injected, at the point where they emerge above the orbit, above the midline of the eyebrow perpendicular to the skin and superficial to the periosteum; the zygomaticotemporal nerves will be blocked using 2 ml of solution midway between the supraorbital and auriculotemporal nerves; the auriculotemporal nerves will be blocked with 3 ml of solution of 1.5 cm in front of the ear at the level of the tragus. The needle will be perpendicular to the skin and 1.5 ml will be injected in the deep fascia, while another 1.5 ml will be superficially injected during the needle extraction; the postauricular branches of the greater auricular nerves will be blocked with 2 ml of solution 1.5 cm posterior to the tragus of the ear, between the skin and bone; the greater, lesser, and third occipital nerves will be blocked with 2 ml of solution injected along the superior nuchal line, approximately midway between the occipital protuberance and the mastoid process. The total volume of the solution used for scalp nerve blocks will be 22 ml in all participants.

### Criteria for discontinuing or modifying allocated interventions {11b}

Prior to providing consent, it will be explained that participation in this clinical trial is voluntary and that each participant has the right to withdraw from the study at any time, without stating reasons, without incurring disadvantages for their future care or benefits. Participants can withdraw from the study at their own request or at the principal investigator’s (PI) discretion. Withdrawal of consent can result in the termination of patient’s participation. No further study-related measures will be carried out. The PI will be responsible for any amendment of the trial. Any protocol amendment will be submitted by PI and approved by the Institutional Review Board (IRB).

### Strategies to improve adherence to interventions {11c}

During preoperative visit, patients will be explained on how to use the PCA pump. The PI will supervise the implementation of the intervention and follow-up throughout. A blinded research assistant will conduct postoperative visits at 2, 4, 8, 12, 16, 20, 24, and 48 h for postoperative data collection and ensure adherence to interventions. The blinded postoperative care staff will also regularly check on participants and will advise them to press the PCA demand button if necessary. To monitor and improve adherence, there will be online updates of PCA drug dosage, press counts, and time of each press at real time.

### Relevant concomitant care permitted or prohibited during the trial {11d}

On arrival to the postanesthesia care unit (PACU) or intensive care unit (ICU), each patient will receive patient-controlled analgesia (PCA) pumps including 100 μg sufentanil and 16 mg ondansetron diluted to 100 mL of 0.9% saline. Postoperatively, when the patient reports a numeric rating scale (NRS) score of 4 or more, or at the request of the patient, patients will be treated with PCA 2 μg bolus, with a lockout interval of 10 min, without continuous background infusion dose or loading dose, and a maximum of 8 μg per hour. The type and doses of postoperative analgesic supplementation will be recorded in detail in the case report form (CRF).

### Provisions for post-trial care {30}

All types of AEs that occur from the day of randomization to the end of follow-up will be reported to the sponsor as soon as possible after the research staff identifies the event. Meanwhile, patients will also be treated as soon as possible if any AEs occur during the trial. The drug combinations, such as the drug name, frequency of use, dosage form, and dose, will be recorded in detail by researchers.

### Outcomes {12}

#### Primary outcome

The primary outcome will be the duration of analgesia, defined as the time between the performance of the block and the administration of the first press of PCA demand button postoperatively.

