**Methods:**

The REDUCE trial is a prospective, single-center, parallel-group randomized controlled trial involving a total of 156 adults scheduled for elective craniotomy with general anesthesia. Patients will be randomly divided among two groups: the control group (*n* = 78) will receive scalp nerve blocks with 0.5% bupivacaine, plus normal saline with epinephrine at 1:200,000; the DEX_4mg_ group (*n* = 78) will receive scalp nerve blocks with 0.5% bupivacaine, plus 4 mg dexamethasone with epinephrine at 1:200,000. The primary outcome will be the duration of analgesia, defined as the time between the performance of the block and the first analgesic request.

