In 2003, Shrestha et al. firstly reported that peripheral dexamethasone significantly prolonged the duration of analgesia of brachial plexus block [26]. Subsequently, the addition of dexamethasone (1~8 mg) was observed to prolong the median duration of analgesia by 27~39% in various nerve blocks (e.g., saphenous nerve block, adductor canal block, thoracic paravertebral block, brachial plexus nerve block) without any unwanted effects [27–36]. Among them, a meta-analysis of optimal dose of perineural dexamethasone suggested that 4 mg of perineural dexamethasone represents an analgesic ceiling dose and higher doses failed to provide additional analgesic duration [34]. The possible mechanisms of perineural dexamethasone prolonging the analgesic time of the peripheral nerve block are by reducing local anesthetics absorption by inducing a degree of vasoconstriction [37] and decreasing activity of C fibers by inhibiting potassium channels [38]. Moreover, there is no evidence of significant neurotoxicity of perineural administration of dexamethasone [39]. On the contrary, in a pioneering study, Jose et al. applied 8 mg dexamethasone as an adjuvant to 0.2% ropivacaine for scalp nerve blocks and reported that perineural dexamethasone did not appear to prolong the analgesic time after supratentorial craniotomy. However, all patients were given 24 mg of oral or intravenous dexamethasone regularly at least 7 days during the perioperative period. Such persistent high doses of systemic dexamethasone possibly masked the role of single local low doses of perineural dexamethasone. The analgesic effect of single dexamethasone for scalp nerve blocks without the background of perioperative glucocorticoid deserves further clarification.

We postulate that without the background of perioperative glucocorticoid, the use of single dexamethasone as an adjuvant to scalp nerve blocks can prolong the analgesic duration, reduce opioid consumption and improve the quality of scalp nerve blocks compared with bupivacaine alone after supratentorial craniotomy. The primary outcome will be the duration of analgesia, defined as the time between the performance of the block and the first analgesic request.

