#### Secondary outcomes

The cumulative amount of sufentanil consumption by PCA at 4, 12, 24, and 48 h postoperatively and the number of participants who have no PCA press will also be documented.The NRS (11-point scale in which 0 = no pain to 10 = worst imaginable pain) will be determined at fixed intervals after the procedure, i.e., 2, 4, 8, 12, 16, 20, 24, and 48 h. An NRS score ≥4 will be considered significant or moderate pain. An NRS score ≥7 will be considered severe pain. Meanwhile, the localization of the site of the pain will also be documented.The GCS [40] will be assessed at predetermined intervals after the procedure, i.e., 2, 4, 8, 12, 16, 20, 24, and 48 h.Postoperative observation: postoperative nausea and vomiting (PONV), bradycardia, hypotension, and emergence delirium within 48 h after surgery will be recorded. Vomiting will be defined as the forceful expulsion of gastric contents, and nausea will be defined as an unpleasant sensation associated with the urge to vomit. Bradycardia will be defined as HR< 60 beats/min in at least two instances more than 5 min apart. Hypotension will be defined as any of the following: systolic BP < 90 mm Hg for 5 min or a 35% decrease in mean arterial blood pressure [41]. Emergence delirium will be assessed by the Sedation Agitation Scale (SAS), a 7-point scale on which a higher score represents greater agitation [42]. The time in the PACU and the length of stay (LOS) will be recorded. The LOS will be defined as the number of nights spent in the hospital after surgery. The postoperative data will be collected by reviewing each patient’s medical record.Postoperative satisfaction: Patient satisfaction will be assessed by the patient satisfaction score (PSS) (0 for unsatisfactory to 10 for very satisfactory) at 2, 4, 8, 12, 16, 20, 24, and 48 h after surgery.

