## Data collection and management

### Plans for assessment and collection of outcomes {18a}

After obtaining written informed consent, baseline data, including age, sex, BMI, intraoperative opioid dose, operation time, anesthesia time, surgical site, tumor types, and tumor size, will be collected by an independent researcher. The PCA press will be recorded by an electronic memory system in real time. The information of PCA press including the first press of PCA demand button and the cumulative amount of sufentanil consumption can be directly extracted. In order to ensure postoperative analgesia quality, an acute pain management team will monitor the pain pump remotely and deal with problems, such as congestion and battery drain, on time. An independent clinical resident who is not involved with the group allocation will complete a follow-up at 2, 4, 8, 12, 16, 20, 24, and 48 h after surgery.

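### The primary event is worded in two ways, and under the operative one (first PCA press) a patient given another analgesic first still counts as having block analgesia

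*Protocol article*

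**What the plan says.** All references are to the protocol article.

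- **Abstract, Methods:** the primary outcome is the duration of analgesia, "defined as the time between the performance of the block and the first analgesic request". Background and rationale {6a} repeats this: "The primary outcome will be the duration of analgesia, defined as the time between the performance of the block and the first analgesic request".
- **Outcomes {12}, Primary outcome:** the interval ends at "the administration of the first press of PCA demand button postoperatively".
- **Assessment and collection of outcomes {18a}:** "The PCA press will be recorded by an electronic memory system in real time"; the first press is extracted from that record.
- **Concomitant care {11d}:** PCA treatment is given "when the patient reports a numeric rating scale (NRS) score of 4 or more, or at the request of the patient". The section then adds: "The type and doses of postoperative analgesic supplementation will be recorded in detail in the case report form (CRF". It does not prohibit other analgesics.
- **Adherence {11c}:** care staff check on patients and "will advise them to press the PCA demand button if necessary".
- **Secondary outcomes:** "the number of participants who have no PCA press will also be documented".

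No section says how a non-PCA analgesic given before the first press enters the primary outcome.

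**The concern.** A request and a press are not the same event. A patient who asks for pain relief and receives a drug outside the pump has reached the endpoint under the abstract and the background. Under the Outcomes section the clock runs on until a press is logged. If none is logged, the patient joins the group with no press, which reads as the best result.

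The block has stopped being sufficient for such a patient, yet the recorded duration is lengthened. If these patients are commoner in the control arm, as the trial hypothesis would suggest, control durations are inflated and the estimated benefit shrinks. Two wordings of the primary event in one document also leave the reader unsure which one the final report will use.

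**Working it through.** **1. The passages side by side**

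| Situation | Abstract and {6a}: first request | Outcomes {12}: first press |
|---|---|---|
| Patient presses unprompted | event | event, same time |
| Patient in pain, staff advise a press, patient presses | event at or near the press | event at the press |
| Patient asks for and gets a non-PCA analgesic, presses later | event at the request | event only at the later press |
| Patient asks for and gets a non-PCA analgesic, never presses | event at the request | no event; counted as no press |

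The definitions part in the last two rows. Section {11d} leaves both rows possible: it records the type of supplementation as well as the dose, and rules nothing out.

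**2. Size**

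The plan has no figure for this point to reproduce. The documents do not say how many patients receive another analgesic first, or how long before the first press. Both are assumptions here.

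Let *p* be the share of an arm given another analgesic first, and *g* the mean gap in minutes from that dose to the first press. Each arm's mean is lengthened by *p × g*. The difference (dexamethasone minus control) is shifted by

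*p*(dex) × *g*(dex) − *p*(control) × *g*(control).

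Equal shares with equal gaps cancel: 10% × 360 = 36 min in both arms gives 36 − 36 = 0. With equal gaps, the shift is the excess share times the gap.

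Inputs for scale, from Sample size {14}: control mean 600 min, SD 240 min, effect 30% of 600 = 180 min, minimal clinically significant difference 60 min, 70 per group. Tests are two-sided at 0.05 ({20a}).

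Example: a 5% excess in control with a 360-min gap gives 0.05 × 360 = 18 min, so 180 becomes 162 min. The standard error is 240 × √(2/70) = 40.57 min.

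- Power at 180 min: Φ(180/40.57 − 1.96) = Φ(2.48) = 99.3%.
- Power at 162 min: Φ(162/40.57 − 1.96) = Φ(2.03) = about 98%.

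(The plan states 90% for 70 per group. These inputs give 99.3%; that mismatch is a separate matter and does not bear on this point.)

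Range, as shrinkage in minutes with resulting power in brackets:

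| Excess share in control | gap 120 min | gap 240 min | gap 480 min |
|---|---|---|---|
| 5% | 6 (99.0%) | 12 (98.5%) | 24 (97.0%) |
| 10% | 12 (98.5%) | 24 (97.0%) | 48 (90.2%) |
| 20% | 24 (97.0%) | 48 (90.2%) | 96 (54.4%) |
| 30% | 36 (94.4%) | 72 (75.9%) | 144 (14.2%) |

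For the shrinkage to reach 60 min at a 360-min gap, the excess would have to be 60/360 = 16.7%.

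These figures apply to a comparison of means and to patients who do press eventually. They do not cover a Wilcoxon-Mann-Whitney comparison, or patients with no press, for whom the gap has no value.

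**The case against.** The strongest reply is that the abstract and background give the concept and the Outcomes section makes it operational. PCA is the only postoperative analgesic named, every patient receives a pump on arrival in the PACU or ICU, and staff prompt patients to press. In this setting a press is how a patient asks for analgesia. The sentence on supplementation follows the PCA regimen, names no other drug and describes no other rescue pathway. A rule for another analgesic given first could be set in the statistical analysis plan, which {20a} says will be fixed before database lock; {17a} blinds the data analysts.

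Most of this stands as a limit on size: request and press probably coincide for most patients. It does not remove the point. The protocol itself states the primary event, states it in two ways, and the operative wording gives a definite and wrong answer for a patient treated outside the pump. An analysis plan that corrected this would be changing the stated endpoint, which goes beyond filling in detail.

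Three stronger readings are tempting but not supported.

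- A reader might infer from {11d} that staff give a PCA bolus at an NRS of 4 or more, which a record of patient presses would miss. No clinician bolus is described, and {11c} has staff advise the patient to press, which is an event.
- A reader might build a shift larger than the 60-min minimal difference, for instance 10% of one arm with a gap of 800 min, giving 80 min. That sets a one-arm shift against a between-arm difference. It also needs a gap of about 13 h, although visits in the first 24 h are at most 4 h apart.
- A reader might assume that every time needed is already collected. Section {11d} names only type and doses, and {30} lists drug name, frequency, dosage form and dose; neither mentions time of administration.

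**Conclusion.** The point holds as a specific defect in the stated primary-endpoint rule. The two wordings are different events, and the operative one counts a patient given a non-PCA analgesic first as having continuing block analgesia.

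The size is unknown because the documents give no rates, and it is probably modest. At a 5% excess and a 360-min gap, both assumed, it is 18 min of a planned 180 min and costs little power. Only combinations near the upper corner of the range would matter much, and nothing in the documents makes them likely. The direction is toward zero if the excess is in the control arm, and away from zero if it is in the dexamethasone arm. The trial's validity does not turn on this, but it should be corrected because it concerns the primary outcome and the remedy is cheap.

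**What to change.** Use one definition in the abstract, Background {6a} and Outcomes {12}. The interval ends at the earlier of:

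1. the first PCA demand press in the pump log, whether or not a dose is delivered;
2. the first dose of any non-PCA analgesic given for postoperative pain.

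Keep first press only as a sensitivity analysis, and report how many patients in each arm had a non-PCA analgesic first, so that the effect of the choice can be seen.

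Cost: a wording change in three places and a CRF field for the time of each non-PCA analgesic dose, since only type and doses are named now. Some recorded durations become shorter. No treatment changes.

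If patients have already been followed up without that time field, the times would have to come from their medical records, where these hold them.

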#### Secondary outcomes

The cumulative amount of sufentanil consumption by PCA at 4, 12, 24, and 48 h postoperatively and the number of participants who have no PCA press will also be documented.The NRS (11-point scale in which 0 = no pain to 10 = worst imaginable pain) will be determined at fixed intervals after the procedure, i.e., 2, 4, 8, 12, 16, 20, 24, and 48 h. An NRS score ≥4 will be considered significant or moderate pain. An NRS score ≥7 will be considered severe pain. Meanwhile, the localization of the site of the pain will also be documented.The GCS [40] will be assessed at predetermined intervals after the procedure, i.e., 2, 4, 8, 12, 16, 20, 24, and 48 h.Postoperative observation: postoperative nausea and vomiting (PONV), bradycardia, hypotension, and emergence delirium within 48 h after surgery will be recorded. Vomiting will be defined as the forceful expulsion of gastric contents, and nausea will be defined as an unpleasant sensation associated with the urge to vomit. Bradycardia will be defined as HR< 60 beats/min in at least two instances more than 5 min apart. Hypotension will be defined as any of the following: systolic BP < 90 mm Hg for 5 min or a 35% decrease in mean arterial blood pressure [41]. Emergence delirium will be assessed by the Sedation Agitation Scale (SAS), a 7-point scale on which a higher score represents greater agitation [42]. The time in the PACU and the length of stay (LOS) will be recorded. The LOS will be defined as the number of nights spent in the hospital after surgery. The postoperative data will be collected by reviewing each patient’s medical record.Postoperative satisfaction: Patient satisfaction will be assessed by the patient satisfaction score (PSS) (0 for unsatisfactory to 10 for very satisfactory) at 2, 4, 8, 12, 16, 20, 24, and 48 h after surgery.

